### Measures

The measures completed at each time point are displayed in Table 3.

The primary feasibility outcomes of this pilot trial will be the number of patients screened, and the percentages of eligible patients recruited and retained at 6-month follow-up. In addition to the study documentation (AUDIT C screening questionnaires, expression of interest and consent forms), detailed logs documenting each patient approached and screened along with the outcome of screening, expression of interest and consent will be kept by each site and will be provided to the NCTU on a monthly basis. A number of tools will assess response variability in key measures proposed to be used in a future definitive trial where the primary outcome would be perioperative drinking status. Baseline alcohol consumption, health-related quality of life and joint functionality will be assessed by the full AUDIT [34], EQ-5D and Western Ontario and McMaster Universities Osteoarthritis Index (WOMAC) Functional Assessment score [46] respectively. Changes in these measures will be assessed with completion of the same measures at follow-up (1–3 days pre-surgery (AUDIT only), 6 weeks post-surgery and 6 months post intervention). Major and minor postoperative complications will be recorded by Clavien-Dindo classification [54] and the Postoperative Morbidity Survey (POMS) [55] collected at 3–5 days post-surgery.

Due to the low-risk nature of the study, adverse events will not be recorded. All serious adverse events (SAEs) excluding those which relate to pre-existing medical conditions, planned rehospitalisation and postsurgical complications which are covered by the trial outcome measures (specifically Clavien-Dindo and POMS) will be recorded by the PI or a delegate on a SAE form which will be sent to the senior trial manager, trial manager, chief investigator and the sponsor. For each SAE, full details in medical terms and a case description will be given along with the event duration, action taken, outcome and seriousness criteria causality in the opinion of the investigator and whether the event is considered expected or unexpected. All safety data collected will be reviewed by the Trial Steering Committee and Data Monitoring Committee.

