Primary outcome(s)	Number of patients screened, and the percentages of eligible patients recruited and retained at 6-month follow-up.
Key secondary outcomes	Alcohol consumption: full AUDIT score Health Related Quality of Life: The EQ-5D Major and minor postoperative complications: Clavien-Dindo classification; Postoperative Morbidity Survey (POMS) Joint functionality: Western Ontario and McMaster Universities osteoarthritis index (WOMAC) Functional Assessment score.

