### Aim

The primary aim of this pilot RCT is:

To estimate rates of patient eligibility, recruitment and retention at 6 months post-assessment in order to assess the feasibility of proceeding to a definitive RCT.

The secondary objectives are:To train healthcare professionals (HCPs) in the delivery of structured screening and brief behavioural intervention to eligible patients in the preoperative assessment setting.To assess completion rates for all data collection tools including measures of alcohol consumption, quality of life and joint functionality.To establish response variability of proposed outcome measures for a definitive trial, which will include drinking status and quality of lifeTo estimate rates of secondary outcomes and perioperative complication rates including bleeding and infectionsTo explore the acceptability of intervention and research methods with HCPs and patients through qualitative interviews.

While this pilot RCT is primarily concerned with recruitment and retention, a definitive RCT would have the primary objective of evaluating the effectiveness of brief behavioural intervention in reducing perioperative alcohol consumption. Secondary objectives would include assessing any resultant changes in secondary outcomes of alcohol perioperative complication rates and quality of life as well as longer-term changes in alcohol consumption at 6 months post intervention.

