	Screening	Visit 1 6–8 weeks pre-surgery	Visit 2 1–2 weeks pre-surgery (intervention arm only)	Visit 3 1 and 3 days pre-surgery	Visit 4 Up to 5 days post-surgery	Visit 5 6 weeks post-surgery	Visit 6 6 months post intervention
Enrolment:							
AUDIT C	X						
Expression of Interest	X						
Consent		X					
Randomisation		X					
Interventions:							
Intervention		X					
Booster			X				
TAU		X					
Assessments:							
AUDIT Baseline		X					
EQ-5D Baseline		X					
AUDIT Outcome			X	X		X	X
EQ-5D Outcome						X	X
WOMAC		X			X		
POMS					X		
Clavien-Dindo					X		
Interview							X

The BA and BI tools were based on the ‘How much is too much?’ Simple Structured Advice, and Extended Brief Intervention tools originally produced as part of the World Health Organization collaborative study on alcohol screening and brief intervention [48], before being adapted for use in the UK [49] and updated [37].

Patients who consent to be contacted for the second ‘booster’ session will be contacted approximately 1 week before surgery to arrange receipt. This will take place either over the telephone or in clinic at the patient’s preference. The HCP delivering the booster session will complete the full AUDIT questionnaire with patients and will aim to review or revise behavioural goals, provide feedback on performance and discuss self-monitoring to increase self-efficacy. The aim of the booster is to reinforce behaviour change by providing an opportunity for participants who had not set a goal or made a plan to reduce their drinking in the initial session the opportunity to do so. For those participants who had set a goal, the booster offers an opportunity to reflect on their experiences since the initial session, receive feedback on their progress and revise or amend their goal if necessary. Such sessions have previously been employed to address limitations presented by busy clinical settings where clinician time may be restricted and participants attention may be elsewhere (such as on their medical care) [50]; however, as booster sessions are not often well attended [51] and findings regarding the added benefit of booster sessions are mixed [52, 53], it was decided that these sessions would be optional rather than required.

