### Follow-up

Baseline measures will be completed at the preoperative assessment visit. Patients will be followed up 1–3 days preoperatively either by telephone or in hospital if admitted the day before surgery; up to 5 days post-surgery while in hospital; at the 6 weeks post-surgery outpatient appointment or by telephone; and 6 months post intervention.

Study data will be entered into the trial MACRO™ database. Access to the MACRO™ database will be granted to site’s PIs, their delegated data entry personnel at sites and NCTU trial management team for monitoring purposes.

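### Table 3 and the Measures text share no follow-up time for WOMAC: the table has it only in hospital within 5 days of surgery, the text at 6 weeks and 6 months

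*Protocol article*

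**What the plan says.** Table 1 of the protocol article (Design section) lists WOMAC among the key secondary outcomes: "Joint functionality: Western Ontario and McMaster Universities osteoarthritis index (WOMAC) Functional Assessment score". The Aim section includes this secondary objective: "To assess completion rates for all data collection tools including measures of alcohol consumption, quality of life and joint functionality".

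Two places then set the timing of WOMAC.

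- **Measures section.** It introduces the baseline instruments with "Baseline alcohol consumption, health-related quality of life and joint functionality will be assessed by the full AUDIT", followed by EQ-5D and WOMAC. The next sentence reads "Changes in these measures will be assessed with completion of the same measures at follow-up (1–3 days pre-surgery (AUDIT only), 6 weeks post-surgery", and the list ends with six months after the intervention. For the early post-operative period it names only Clavien-Dindo and POMS, "collected at 3–5 days post-surgery".
- **Table 3 (placed in the Intervention section).** The WOMAC row is marked at Visit 1 and in the column headed "Visit 4 Up to 5 days post-surgery". The cells for Visit 5 (6 weeks) and Visit 6 (6 months) are empty. The Follow-up section describes the Visit 4 contact as "up to 5 days post-surgery while in hospital".

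The Measures section also points the reader to the table: "The measures completed at each time point are displayed in Table 3". The Statistical analysis section repeats that pointer.

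**The concern.** The article gives two incompatible schedules for one key secondary outcome and presents the table as the reference for what is collected when. Anyone who builds visit forms from the table would schedule no WOMAC at 6 weeks or 6 months. Anyone who works from the text would schedule it at both and not at Visit 4.

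One purpose of this pilot is to test instruments before a definitive trial. The Statistical analysis section says that completeness of each tool, and any difference in completion between arms, will guide which tools are kept. For WOMAC that information would be missing at the two later times named in the text. A patient-reported questionnaire that was not scheduled cannot be recovered afterwards.

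**Working it through.** **1. The plan's own figure.** The only sample-size calculation is 30 per arm at 6 months with 25% loss: 30 / (1 − 0.25) = 40 per arm, and 2 × 40 = 80 in total. This reproduces the stated target. WOMAC does not enter it.

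**2. Is the mismatch an artefact of reading the PDF?** Table 3 has seven time columns: Screening and Visits 1 to 6. Counting cells in each row gives:

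| Row | Marked at | Agrees with the text? |
|---|---|---|
| AUDIT C | Screening | Yes |
| AUDIT Outcome | Visits 2, 3, 5, 6 | Yes (booster, pre-surgery, 6 weeks, 6 months) |
| EQ-5D Outcome | Visits 5, 6 | Yes |
| POMS | Visit 4 | Yes |
| Interview | Visit 6 | Yes |
| WOMAC | Visits 1, 4 | Baseline yes; follow-up no |

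Each of these rows has the full seven cells, and every row other than WOMAC falls where the text places it. A column shift in the reading of the table is therefore not a plausible explanation.

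**3. Post-baseline WOMAC times, side by side.**

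| Time | Measures text | Table 3 |
|---|---|---|
| Before surgery | No (AUDIT only) | No |
| Visit 4, within 5 days after surgery | Not named (Clavien-Dindo and POMS only) | Yes |
| Visit 5, 6 weeks | Yes | No |
| Visit 6, 6 months | Yes | No |

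The text has two follow-ups, the table has one, and the overlap is zero.

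**4. Forms at stake if the table governs.**

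- Ceiling with no attrition: 80 patients × 2 visits = 160 forms.
- Allowing for the plan's 25% loss: 80 × 0.75 = 60 patients at 6 months. The number at 6 weeks is not stated. Assuming that it lies between 60 and 80, the total is 60 + 60 = 120 to 60 + 80 = 140 forms.
- Forms scheduled under the table at those two visits: 0.
- Forms scheduled at Visit 4 under the table: up to 80; under the text: 0.

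**The case against.** The mismatch itself is hard to dispute. The case on the other side concerns its consequences, and much of that case stands.

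- **A reader might infer that following the table leaves no usable joint-function follow-up.** The documents do not support this. Visit 4 would still give one post-operative WOMAC per patient, with a completion rate and a standard deviation. Nothing in the article says that an in-hospital score is uninformative. It is reasonable to doubt that such a score can stand in for function at 6 weeks or 6 months, but that is a judgement.
- **A reader might infer that a secondary objective fails.** The completion-rate objective sets no time for WOMAC and could be met in part from baseline and Visit 4. The objective on response variability names drinking status and quality of life, not joint function. The later WOMAC times appear only in the Measures section.
- **A reader might infer that data were or will be lost.** This is a condensed article. The full protocol, the case report forms and the database are not shown, and the error may be confined to the published table or sentence.
- **A reader might infer that the Visit 4 mark is plainly a misprint.** The documents do not settle this. The mark may be misplaced, the sentence in Measures may be too general, or WOMAC may have been meant at Visit 4 as well as later.

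The objection does not remove the contradiction. The article states both schedules, so this is not detail left to another document, and twice it sends the reader to the table.

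**Conclusion.** This is an internal inconsistency that should be fixed. It is not a flaw that undermines the pilot. Table 3 and the Measures section share no post-baseline WOMAC time point.

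The consequence depends on which of the two is followed. If sites follow the table, no WOMAC is collected at 6 weeks or 6 months. The change in joint function described in Measures, and WOMAC completion and variability at those times, then cannot be reported. That would be up to 160 questionnaires with no attrition, or about 120 to 140 under the plan's own loss allowance and the assumption about 6-week attendance given above. One in-hospital WOMAC would remain.

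Screening, recruitment, retention and the target of 80 do not depend on WOMAC. The outline of the definitive trial in the Aim section does not list joint function among its objectives, which also limits the weight of the point. The conclusion rests on reading the AUDIT-only restriction as applying to the pre-surgery contact alone, which is how the sentence is built and how the EQ-5D row of the table treats it.

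**What to change.** Reconcile Table 3 with the Measures section:

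1. Add WOMAC to Table 3 at Visit 5 (6 weeks) and Visit 6 (6 months), in line with the text and with the EQ-5D Outcome row.
2. Have the sponsor confirm whether the Visit 4 WOMAC is intended. If it is, add it to the Measures text; if not, remove the mark.
3. Check that the visit case report forms and the trial database carry the same schedule.

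If the sponsor in fact intended Visit 4 as the only follow-up, the sentence in Measures must change instead, and the article should say that change in joint function will not be assessed at 6 weeks or 6 months.

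The cost is a correction to one table, a check of the forms, and one extra questionnaire at two visits where AUDIT and EQ-5D are already collected. No change to sample size or to the primary outcomes is needed.

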### Follow-up

Baseline measures will be completed at the preoperative assessment visit. Patients will be followed up 1–3 days preoperatively either by telephone or in hospital if admitted the day before surgery; up to 5 days post-surgery while in hospital; at the 6 weeks post-surgery outpatient appointment or by telephone; and 6 months post intervention.

Study data will be entered into the trial MACRO™ database. Access to the MACRO™ database will be granted to site’s PIs, their delegated data entry personnel at sites and NCTU trial management team for monitoring purposes.

### Qualitative work

Qualitative, in-depth, one-to-one semi-structured interviews will be conducted with both patient and HCP participants. Patients who indicate at initial consent that they would be happy to participate in a qualitative interview will be asked again if they are willing to take part in an interview as part of the 6-month post-intervention follow-up. Patients still willing to participate in an interview will be provided with an interview-specific information sheet by email or post (dependent on patient preference) at least 24 h before the interview is due to take place. Following patient recruitment and intervention delivery, HCPs involved in screening and/or intervention delivery will also be invited to take part in a qualitative interview. These interviews will be conducted by a Research Associate (EL) and will use a semi-structured topic guide to explore HCP and patient experiences of being involved in the trial, the acceptability of screening and intervention tools/materials, barriers and facilitators to screening and intervention delivery and the feasibility of delivering screening and intervention in the preoperative assessment clinic. Topic guides will include key questions and prompts but will be left flexible enough for discussion to include issues of importance to the participant or issues arising from previous interviews. All interviews will be digitally recorded, with consent, and transcribed verbatim.

### Planned analysis

#### Statistical analysis

The measures collected at each time point are displayed in Table 3. Analysis will be descriptive in nature. The number of patients approached, screened, found to be eligible and recruited (as documented in screening logs) will be reported. Screening and eligibility rates will be assessed.

The primary feasibility outcome is recruitment and retention to 6-month follow-up. Systematic reviews and meta-analyses of alcohol brief intervention trials show that follow-up rates vary with mean follow-up rates of approximately 75% [56, 57] though rates of follow-up for older adult populations may be higher (e.g. [58]). It was therefore decided to allow for a loss to follow-up of 25%. Based on current recommendations for external pilot trials [59], 30 patients per arm at 6-month follow-up were required to estimate the critical parameters to the necessary degree of precision with a continuous primary outcome. The pilot trial will therefore aim to obtain data from 40 participants in each trial arm at baseline. As follow-up rates vary between trials of alcohol brief interventions, the target recruitment sample size will be kept under review, and recruitment will cease when we estimate that 60 patients will provide data at 6 months post intervention.

Secondary outcomes of compliance with randomisation (whether or not participants received the intervention when randomised to the intervention condition), and data completion of baseline measures will also be reported. Non-completers will be characterised.

The pilot feasibility trial will also assess performance of potential outcome measures for a definitive trial. We will ascertain data completeness of the study tools and any potential bias in the completion of follow-up data (assessing if completion rates on each clinical outcome are markedly different in either trial arm), to inform the choice of tools for a future trial.

The majority of data will be presented in simple descriptive tables presenting percentages, means and standard deviations or five-number summary (the minimum, first quartile, median, third quartile, and maximum) as appropriate, for each arm of the study. This information will be used to inform the design, choice of primary outcome, necessary sample size and approach to the analysis, of the future definitive trial.

### Qualitative analysis

Qualitative data from HCP and patient interviews will be used to assess the acceptability of screening, intervention and research methods. Anonymised transcripts will be analysed using Framework analysis [60]. This is a recommended approach for qualitative health research with objectives linked to quantitative investigation [61]. NVivo software will be used to aid indexing and charting. The data will be repeatedly read and coded independently by two researchers (EL, KH) within a framework of a priori issues and those identified by participants (patients or HCPs) or emerging from the data. Any divergence between coders will be discussed on an on-going basis to inform the analysis and resolve divergence in their interpretations of the data. Analysis will be discussed at regular meetings of the research team to identify areas for closer consideration (including negative case analysis) and to enhance credibility of the thematic framework and interpretation [61, 62].

Framework analysis of the qualitative data will explore influences on patient recruitment, implementation, receipt of the study interventions and data collection methods. Analysis of the likelihood of embedding study interventions in clinical practice (HCP data) will be informed by Normalisation Process Theory [63]. This model considers factors that affect implementation in four key areas; how people make sense of a new practice (coherence); the willingness of people to sign-up and commit to the new practice (cognitive participation); their ability to take on the work required of the practice (collective action); and activity undertaken to monitor and review the practice (reflexive monitoring). The approach is increasingly used in studies of the implementation of interventions in health care (www.normalizationprocess.org). Analysis will consider how well the behavioural intervention is introduced and incorporated for both patients and HCPs.

### Fidelity analyses

Consultations with a participating patient will be audio recorded to allow an assessment of skill acquisition and fidelity of delivery post-training. Audio recordings will be transcribed verbatim. A Research Associate (EL) trained in the use of the Behaviour Change Taxonomy Version 1 (BCT v1) and an expert coder (LA) will independently code all consultation transcripts to assess skill acquisition (for feedback purposes) and fidelity of delivery of each specific BCT. A coding frame/fidelity checklist based on the BCTv1 will be used to identify whether each BCT was delivered faithfully as planned. Where discrepancies in coding exist, the RA and expert coder will meet to resolve these via discussion. The percentage of positive agreement will be calculated to assess inter-rater reliability.

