Each preoperative assessment HCP who has been trained will aim to conduct a minimum of four patient consultations where the intervention is delivered in order to facilitate full engagement with intervention delivery and allow feedback on fidelity of delivery. Audio recordings will be made of all intervention sessions where the patient provides consent. All recordings will be transcribed verbatim before being deleted from the recording device. All anonymised transcripts will be assessed for fidelity of delivery by two members of the research team (EL and LA) using a standardised checklist of 18 BCTs and 5 behaviour change counselling techniques. As the intervention is designed to allow tailored delivery, assessors will first identify if each item was appropriate before assessing if it was delivered. Feedback (constructed by the research associate (EL) and health psychologist (LA)) regarding skill acquisition and fidelity of delivery will be provided to HCPs for the second and fourth intervention sessions they deliver before any subsequent consultations where the intervention is delivered take place. Where patients in sessions 2 and/or 4 do not consent to recording, fidelity of delivery assessments will be conducted and feedback provided for the next recorded session (where a patient does provide consent). If required (i.e. where fidelity of delivery falls below the 80% threshold, based on the percentage of items assessed as ‘appropriate’ that were identified as delivered), the research associate (EL) will provide an additional, one-to-one, face-to-face training session, lasting up to 1 h to focus on components of the intervention that were omitted when it may have been appropriate to deliver them.

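### Positive agreement alone does not show that the fidelity coding is reliable: it is not corrected for chance and leaves out agreement on 'not delivered'

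*Protocol article*

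**What the plan says.** The Fidelity analyses section of the protocol article describes two coders, a research associate and an expert coder, who "will independently code all consultation transcripts to assess skill acquisition (for feedback purposes) and fidelity of delivery of each specific BCT". Disagreements are settled jointly: "Where discrepancies in coding exist, the RA and expert coder will meet to resolve these via discussion". The section then gives its only measure of reliability: "The percentage of positive agreement will be calculated to assess inter-rater reliability". It attaches no formula, acceptance level, chance-corrected coefficient or negative agreement to this.

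The section Participants—healthcare professionals describes what is coded. Transcripts are assessed "using a standardised checklist of 18 BCTs and 5 behaviour change counselling techniques". The judgement has two steps: "assessors will first identify if each item was appropriate before assessing if it was delivered". Extra one-to-one training follows "where fidelity of delivery falls below the 80% threshold, based on the percentage of items assessed as ‘appropriate’ that were identified as delivered". That session concentrates on components that were left out although delivering them may have been appropriate.

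**The concern.** An inter-rater statistic should tell the reader whether two people applying the checklist to the same transcript reach the same codes more often than their general tendency to tick 'delivered' would produce. Positive agreement does not separate the two. When most items are ticked, it is high even for coders who agree only by chance.

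It also ignores the cell in which both coders say 'not delivered'. That matters here because retraining is directed at omissions. Whether the coders recognise the same omissions is a question the chosen index does not answer directly.

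What is at stake is the claim that the pilot can make about its fidelity checklist. According to the Discussion, the fidelity assessments will help to refine the intervention before a definitive trial. A figure of 85% or 90% would look reassuring in that report, yet could go with weak agreement beyond chance.

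**Working it through.** The article states no agreement figure, so there is none to reproduce. The check asks what the named index would show for coders who agree only by chance, and what a given value implies.

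**Inputs.** From the article: two independent coders; 18 + 5 = 23 items per transcript; positive agreement as the index. Assumed: the rate p at which each coder marks counted items as delivered. I use p = 0.80 for illustration.

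**Notation (proportions of items).** a = both say delivered; b, c = one says delivered and the other does not; d = both say not delivered. Positive agreement PA = 2a/(2a+b+c). Negative agreement NA = 2d/(2d+b+c). Kappa = (po − pe)/(1 − pe), with po = a + d.

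**Chance value.** For independent coders with the same rate p: a = p², b = c = p(1−p), d = (1−p)². Then PA = 2p²/[2p² + 2p(1−p)] = p. At p = 0.80: a = 0.64, b + c = 0.32, d = 0.04, so PA = 1.28/1.60 = 80% and NA = 0.08/0.40 = 20%. A simulation of 40 transcripts × 23 items (4000 runs; 40 assumes one recorded session per intervention patient) gave a mean of 80.0%, with 95% of runs between 77.7% and 82.2%.

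**What a reported value implies.** With both rates at 0.80, a = 0.80 × PA, b = c = 0.80 − a, d = 1 − a − 2b, and pe = 0.80² + 0.20² = 0.68.

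| PA | a | b = c | d | po | kappa | NA |
|---|---|---|---|---|---|---|
| 80% | 0.64 | 0.16 | 0.04 | 0.68 | 0.00 | 20% |
| 85% | 0.68 | 0.12 | 0.08 | 0.76 | 0.25 | 40% |
| 90% | 0.72 | 0.08 | 0.12 | 0.84 | 0.50 | 60% |
| 95% | 0.76 | 0.04 | 0.16 | 0.92 | 0.75 | 80% |

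With equal rates this reduces to kappa = (PA − p)/(1 − p). The same PA of 90% is therefore kappa 0.80 at p = 0.50, 0.50 at p = 0.80 and 0 at p = 0.90. The index cannot be interpreted without the delivered rate.

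**Sensitivity to what the article leaves open.**
- Other formula: a/(a+b+c) has a chance value of 0.64/0.96 = 66.7% at p = 0.80.
- Unequal rates: chance PA = 2p₁p₂/(p₁+p₂), which is 1.12/1.50 = 74.7% for 0.8 and 0.7, and 1.44/1.70 = 84.7% for 0.8 and 0.9.
- All items counted, with 80% of the appropriate ones delivered and the others coded not delivered: p = 0.64, 0.48 or 0.40 if 80%, 60% or 50% of items are appropriate, and the chance value falls to the same figures.

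**The 'appropriate' step.** If all 23 items are appropriate and 18 are delivered, fidelity is 18/23 = 78.3%, below the threshold. If one undelivered item is judged not appropriate, it is 18/22 = 81.8%, above it. Agreement on this first step is therefore worth knowing too.

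**Alternative coefficients under chance coding.** At p = 0.80, PABAK = 2(0.68) − 1 = 0.36 and Gwet's AC1 = (0.68 − 0.32)/(1 − 0.32) = 0.53. At p = 0.90, where po = 0.82, they are 0.64 and (0.82 − 0.18)/(1 − 0.18) = 0.78. Only Cohen's kappa is zero.

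**The case against.** The strongest reply is that nothing in the trial turns on this index. No acceptance level is attached to it. Every transcript is double coded, one coder is an expert, and disagreements are resolved by discussion, so the fidelity scores are consensus scores. Replacing the coefficient would change no score, no training decision and no feasibility result. This stands, and it limits the severity.

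A second reply is that the 80% base rate is not the plan's. A reader might infer from "where fidelity of delivery falls below the 80% threshold" that about 80% delivery is expected, and hence that chance agreement will be 80%. The article does not support that: the figure is a trigger for extra training, neither a forecast of delivery nor a benchmark for coders. The chance value also depends on formula, margins and denominator, and the readings above run from 40% to about 85%. This stands too, so 80% is used here only as an illustration.

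Third, the choice of coefficient involves trade-offs. Kappa is unstable at high prevalence, and the usual high-prevalence alternatives are themselves well above zero for chance coding. That is a reason to report several quantities together; it does not justify positive agreement on its own.

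Finally, a condensed article may leave the denominator and the coverage of the 'appropriate' step to the full protocol. Agreed: their absence is not held against the plan. The index itself, however, is a stated choice.

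**Conclusion.** The concern holds as a minor point. The one reliability measure that the article names is not chance-corrected and omits agreement on 'not delivered'. If both coders mark 80% of counted items as delivered, and positive agreement has its usual definition, then 80% is the chance value, 85% means kappa 0.25 with negative agreement of 40%, and 90% means kappa 0.50 with 60%. The size depends on that assumed rate, on equal coder margins and on the items counted.

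Two stronger readings are not supported. One is that positive agreement can never show reliable coding, or is bound to be high whatever its quality. At the same 80% rate, 95% corresponds to kappa 0.75, so the index is informative once the delivered rate stands beside it. The other is that retraining would be wrongly triggered or withheld. Those decisions rest on the fidelity score, not on the agreement index. The primary feasibility outcomes (screening, recruitment and retention) are not touched.

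**What to change.** In Fidelity analyses, state that reliability is computed from the two coders' independent codes as they stood before discussion. Report Cohen's kappa with a 95% confidence interval, positive agreement, negative agreement and each coder's delivered rate. Do this for the 'delivered' judgement, naming the formula and the items counted, and likewise for the 'appropriate' judgement, which sets the denominator of the fidelity percentage. PABAK or AC1 may be added as supplements but should not replace kappa, given their values under chance coding.

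The cost is a few lines of analysis. Independent double coding of all transcripts is already planned, so no further coding is needed, provided that the pre-discussion codes are kept. The downside is that kappa becomes unstable when nearly every item is delivered, so it should be read beside positive and negative agreement and the delivered rates.
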